### Plans to give access to the full protocol, participant-level data, and statistical code {31c}

The complete trial protocol and statistical code used for analyses will be made publicly available following publication of the primary results. Following publication of all study results, deidentified participant-level data may be made available upon reasonable request to the principal investigator, or in the case of published works, through the corresponding author.

## Oversight and monitoring

### Composition of the coordinating centre and trial steering committee {5d}

The coordinating trial centre is located at the Royal Adelaide Hospital. The Trial Steering committee (TSC) is co-chaired by the Principal Investigator (PI) at each study site and includes the trial associate investigators. The TSC is responsible for the study conception, drafting, and completion of the study protocol and associated documents, recruitment plan, data monitoring and integrity, end point adjudication, and approving publications arising from the study.

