### Management of COVID-19-positive participants during the trial

Study participants who returned a positive COVID-19 result during the trial will be managed in consultation with their treating transplant unit as per local best practice. Participants who contract COVID-19 following randomisation but prior to a third vaccination may have their third vaccine dose delayed. Where possible, participants will be asked to continue with their allocated treatment regimens and attend study visits and follow-up. Positive COVID cases will be excluded from the primary analysis as SARS-CoV-2 infection will confound assessment of the primary outcome measure.

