### Concealment mechanism {16b}

The allocation sequence is contained and administered centrally through an external web-based randomisation module contained within a purpose-built Research Electronic Data Capture (REDCap) data management platform. The randomisation algorithm and treatment allocation are not accessible to study investigators or research staff.

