### Implementation {16c}

The allocation sequence will be generated by an independent and blinded statistician. Trained study investigators will enrol participants, at each study site, and will perform randomisation via the web-based platform and assign the intervention to each participant.

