## Assignment of interventions: blinding

### Who will be blinded {17a}

Given the significant changes in prescribed immunosuppression, neither the study participants nor clinical staff will be blinded to treatment allocation. Scientific staff performing the laboratory assays for primary and secondary outcomes will be blinded to patient treatment allocation.

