### If blinded, circumstances under which unblinding is permissible, and procedure for revealing a participant’s allocated intervention during the trial {17b}

The design is open label with only outcome assessors being blinded so unblinding will not occur.

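### The protocol says outcome assessors are blinded, but clinical end points are adjudicated by a committee of site investigators who can be expected to know the arm, and two COVID-19 exclusion rules leave a few primary-analysis exclusions open to discretion

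*Protocol article*

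**What the plan says.** All references are to the protocol article.

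- **Who is blinded {17a}:** "neither the study participants nor clinical staff will be blinded to treatment allocation". The only people named as blinded are those who run the laboratory assays for the primary and secondary outcomes.
- **Unblinding {17b}:** "The design is open label with only outcome assessors being blinded so unblinding will not occur".
- **Implementation {16c}:** trained study investigators enrol participants and "will perform randomisation via the web-based platform and assign the intervention to each participant".
- **Steering committee {5d}:** the committee is "co-chaired by the Principal Investigator (PI) at each study site and includes the trial associate investigators". Its duties include "data monitoring and integrity, end point adjudication, and approving publications arising from the study". The section does not list which end points are adjudicated and names no independent or masked member.
- **Management of COVID-19-positive participants:** "Positive COVID cases will be excluded from the primary analysis".
- **Statistical methods {20a}:** the exclusion from the primary analysis is tied to a positive PCR.
- **Secondary outcome measures {12}:** COVID-19 may be established by PCR, by a rapid antigen test accompanied by symptoms, or by anti-nucleocapsid antibody at the primary assessment. Acute rejection shown on biopsy and return of the original kidney disease are also listed.

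**The concern.** Anyone who adjudicates an end point is assessing an outcome. The unblinding section therefore makes a claim that covers the steering committee, yet the committee is drawn from investigators who assign treatment or work in the unblinded clinical setting. A reader who relies on that section would take the clinical end points to be assessed blind, and nothing else in the article supports this.

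Two things are at stake. First, clinical end points that involve some judgement can be decided with the arm known. Second, COVID-19 status removes participants from the primary analysis, and the article gives that rule in two forms of different breadth. Where a case falls between them, someone has to choose, and no section requires the choice to be made without knowledge of the arm.

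**Working it through.** **Step 1. Can the adjudicators be expected to know the arm?** Put four sections side by side. Implementation {16c} has investigators randomising and assigning the intervention. Who will be blinded {17a} leaves clinical staff unblinded. Steering committee {5d} puts the site principal investigators in the chair and associate investigators among the members. Concealment {16b} says "The randomisation algorithm and treatment allocation are not accessible to study investigators or research staff". Taken alone, that last sentence points the other way. Read with {16c} and {17a}, it can only describe concealment before assignment, because the people who assign an open-label drug switch know what they assigned. So yes.

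**Step 2. Does the blinding statement hold for each outcome?**

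| Outcome | Decided by | Supported as blind? |
|---|---|---|
| Live-virus neutralisation (primary) | assay against a fixed threshold | yes, {17a} |
| Anti-RBD IgG, T-cell measures, anti-nucleocapsid antibody | assay | yes, on the wording of {17a} |
| COVID-19 by rapid antigen test with symptoms | test plus a symptom judgement | no |
| Acute rejection on biopsy | biopsy, then classification | not stated |
| Recurrence of the original kidney disease | clinical judgement | no |

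The statement in {17b} is accurate for the assay outcomes and unsupported for the last three rows.

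**Step 3. Where do the two exclusion rules differ?**

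| Participant | Management of COVID-19-positive participants | Statistical methods {20a} |
|---|---|---|
| PCR positive | excluded | excluded |
| Rapid antigen positive only | excluded if counted as a case | kept |
| Anti-nucleocapsid positive only | excluded if counted as a case | kept |

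Only the last two rows leave discretion. The Discussion and Trial status sections report rising community prevalence, so such cases are foreseeable. The article does not say how many there were.

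**Step 4. How much could a few exclusions matter?** The article states no expected response rate, so this is an illustration on an assumed count.

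- Evaluable per arm: 60 × (1 − 0.10) = 54, from Sample size {14}.
- Assumed responders: 24, so the rate is 24/54 = 44.4%.
- Removing *k* responders gives (24 − *k*)/(54 − *k*). With *k* = 3: 21/51 = 41.2%, a change of −3.3 points.
- Removing *k* non-responders gives 24/(54 − *k*). With *k* = 3: 24/51 = 47.1%, a change of +2.6 points.

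If the other arm is untouched, the between-arm difference moves by the same amount. Against the target difference of 25 points this is 2.6/25 = 10% to 3.3/25 = 13%. Each exclusion weighs more if fewer than 54 per arm were evaluable, which is possible because recruitment closed before reaching 120.

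**The case against.** The strongest reply is that the primary result is well protected. It is a threshold on an assay run by blinded staff, and the statistical section removes participants on a laboratory trigger that needs no committee. PCR and antibody results are test results, a rapid antigen case still needs a positive test, and rejection needs a biopsy. The unblinding section is one line that follows directly on a precise statement of who is blinded, so its wording may simply refer back to laboratory staff. The committee is said to include the associate investigators, which is not an exhaustive list. Procedural detail on masking may sit in the full protocol, which is not shown.

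Most of this stands, and it limits the point. It does not remove the unrestricted claim in {17b}, the assignment of adjudication to arm-aware investigators, or the mismatch between the two exclusion rules, all of which are printed in the article.

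Several stronger readings are tempting but not supported:

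- **That unblinded investigators decide membership of the primary analysis set.** No section gives analysis-set exclusions to the committee.
- **That exclusions might be decided with titres in view.** Nothing says the committee sees neutralisation results beforehand.
- **That three decisions could move the effect by 5.9 points.** That figure is 47.1 − 41.2, the gap between two opposite manipulations of the same arm. From the starting rate, each moves it by about 3 points.
- **That one or two exclusions would overturn the conclusion.** With assumed results of 32/54 and 41/54, the uncorrected chi-square p is 0.064, and dropping one sirolimus non-responder gives 0.044. That follows from placing the assumed result beside 0.05 and shows nothing specific to adjudication.
- **That tolerance of sirolimus is another blinding failure.** It exists in one arm only.

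**Conclusion.** The concern holds in a limited form. The blinding claim in {17b} is broader than {17a} supports, and clinical end points needing some judgement (COVID-19 by rapid antigen test with symptoms, rejection, disease recurrence) can be adjudicated knowing the arm. The neutralisation assay is not affected. Because the two COVID-19 exclusion rules differ, a small number of exclusions from the primary analysis could also be discretionary. On the assumed 24/54, three of them in one arm shift its rate by 2.6 to 3.3 points.

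This rests on reading the principal and associate investigators as arm-aware, which {16c} and {17a} make very likely, and on an assumed responder count used only for scale. Nothing in the article suggests that any decision was in fact biased. The point merits correction because the remedy is cheap, not because the primary result is in serious doubt.

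**What to change.** 1. Have the committee adjudicate COVID-19 status where it needs judgement, rejection and disease recurrence on case files with arm, immunosuppressant names and drug levels removed, where feasible by members from the other site.
2. Reconcile the section on COVID-19-positive participants with Statistical methods {20a} into one exclusion definition that says how cases positive only by rapid antigen test or only by anti-nucleocapsid antibody are treated. Apply it and lock the decisions before results are linked to allocation.
3. Limit the statement in {17b} to outcomes measured by laboratory assay.
4. The last visit was in April 2022 and the article appeared in September 2022, so locking may no longer be possible. If data are already unmasked, report which adjudications and exclusions were made with knowledge of the arm.

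The cost is masking a small number of files and fixing an order of data release, with no extra staff. Some cases may remain partly recognisable. Masking also cannot undo arm-aware decisions by treating clinicians about whom to test or biopsy.

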### Composition of the data monitoring committee, its role and reporting structure {21a}

A data safety monitoring board has not been established and was not warranted in this study, given the short duration of the intervention and follow-up. The TSC is responsible for the scientific integrity of the trial and will monitor safety and operational data and will fulfil reporting obligations to the trial sponsor.

### Adverse event reporting and harms {22}

All protocol deviations and AEs will be documented, regardless of their potential relationship to the study intervention. AEs will be recorded using an adaptation of the National Institute of Health’s Common Terminology Criteria for Adverse Events by a study team member on an eCRF. Recorded information on each AE will include a descript of the AE, the onset date, duration, the resolution of the AE, the severity and seriousness, any action taken as a result of the AE, the outcome of the AE, and the likelihood of the relationship of the AE to a study intervention. Screening for adverse events will occur during each study visit and during scheduled clinical follow-up with their treating nephrologist and will be captured up to 7 days following the final study visit. Adverse events following immunisation (AEFIs) with the exception of mild and/or short-lived symptoms will be reported to the Therapeutic Goods Administration (TGA). Serious adverse events (SAEs) will be reported to the trial sponsor with 24-h of the study team being made aware of the event.

### Frequency and plans for auditing trial conduct {23}

There are no plans for trial audit given the short duration of the trial intervention and follow-up.

### Plans for communicating important protocol amendments to relevant parties (e.g. trial participants, ethical committees) {25}

Amendments to the study protocol will be approved by the human research ethics committee (HREC) at the coordinating trial centre, followed by local site governance prior to implementation. The trial registration information contained with the Australia New Zealand Clinical Trial Registry (ANZCTR) will be updated with any protocol modifications.

## Dissemination plans {31a}

The results of the RIVASTIM-inulin trial will be published in peer-reviewed academic journals and presented at national and international scientific meetings. Additionally, a lay summary containing the study aim, salient findings, conclusions, and a take home message will be prepared and distributed to trial participants, research staff, and interested members of the transplant community. The lay summary will be distributed via direct approaches to trial participants and be made widely available through electronic media including newsletters, social media, and websites.

## Discussion

Interventions to improve COVID-19 vaccine responses in transplants recipients are required. Preclinical studies and observational findings in KTRs suggest that the mTOR inhibitor sirolimus may enable enhanced immunological responses to COVID-19 vaccination, as compared to standard of care immunosuppression which includes mycophenolate.

This multi-centre, prospective, randomised, controlled trial has been designed to measure the effect of temporarily modifying maintenance immunosuppression with sirolimus, in conjunction with withdrawal of mycophenolate, on correlates of immune protection from COVID-19. The trial uses a pragmatic, established immunosuppression protocol to boost vaccine responses. Sirolimus is a commonly used immunosuppressant that is well tolerated at trough target levels of 3–6 ng/mL. As such, improved immunity in the treatment arm would provide strong justification for the use of sirolimus switch to enhance vaccine-induced protection against COVID-19 among KTRs.

There are limitations to a rapidly designed trial in the context of the COVID-19 pandemic. At the commencement of the trial, Australia had a largely SARVS-CoV2-naïve population with minimal community transmission. However, with the easing of social restrictions and border controls there is increasing community prevalence. Thus, trial recruitment may be limited by the prerogative to not delay booster vaccination in a vulnerable population, and in the loss of potential recruits to either having already had booster vaccination or having developed COVID-19. Additionally, while this study will provide a targeted strategy for immunosuppression modification, it will not be possible to discern the individual contributions of withdrawing mycophenolate versus addition of sirolimus on the immune response.

### Trial status

**Table Tabb:** 

Protocol version	3.0
Protocol date	3 October 2021
Recruitment start date	8 November 2021
Anticipated recruitment end date	15 February 2022
Reason for submission after recruitment cessation	Early recruitment closure before submission as unable to enrol target 120 patients due to (1) reducing number of eligible participants with ongoing vaccine roll-out and (2) increasing community prevalence of COVID-19 making further delays in vaccination due to trial participation unacceptable

## Data Availability

Datasets and results generated as part of this study will be jointly owned by Central Adelaide Local Health Network, the University of Adelaide, and the Royal Prince Alfred Hospital (RPA, SLHD). Deidentified participant data may be made available from the corresponding author of published works upon reasonable request and submission of a research plan of appropriate scientific merit and ethical standing.

## Abbreviations

AEFI: Adverse events following immunisation
AEs: Adverse events
ANZCTR: Australia and New Zealand Clinical Trials Registry
CALHN: Central Adelaide Local Health Network
CKD-EPI: Chronic Kidney Disease - Epidemiology Collaboration
eCRF: Electronic case report form
eGFR: Estimated glomerular filtration rate
EQ-5D: EuroQol five dimensions
GCP: Good Clinical Practice
GSRS: Gastrointestinal symptom rating scale
HREC: Human research ethics committee
KTRs: Kidney transplant recipients
mTOR: Mechanistic target of rapamycin
mTORi: Mechanistic target of rapamycin inhibitor
mTORC1: Mechanistic target of rapamycin complex 1
RBD: Receptor-binding domain
REDCap: Research Electronic Data Capture
RIVASTIM: Rapamycin and inulin for booster vaccine response stimulation
SAEs: Serious adverse events
SARS-CoV-2: severe acute respiratory syndrome coronavirus 2
SCFA: Short-chain fatty acids
SLHD: Sydney Local Health District
TGA: Therapeutic Goods Administration
TSC: Trial steering committee
